**Dose Modification of KN026**

Whenever a subject experiences a protocol-specified  $\geq$  Grade 3 toxicity related to KN026 treatment (except for laboratory abnormalities that are not clinically significant or do not meet the criteria for AEs listed below), KN026 is required to be interrupted until the treatment-related toxicity resolves to  $\leq$  Grade 1. Guidelines for dose modification of KN026 are provided in Table 3.

To monitor asymptomatic pneumonitis (CTCAE Grade 1), a chest CT scan is required. Additional chest X-rays or CT scans are required clinically. Management and dose modification of pneumonitis suspected to be related to KN026 are provided in Section 6.2.3.2.

LVEF and cardiovascular-related clinical symptoms and signs need to be monitored during treatment with KN026. Management and dose modification of cardiotoxicity suspected to be related to KN026 are described in Section 6.2.3.3.

If KN026 is discontinued due to an AE, the investigator should decide whether to continue treatment with KN046 in accordance with Section 6.1.4.1.

**Table 3 Guidelines for Dose Modification of KN026**

| Treatment-Related Toxicity            | Severity                                                                                                                                                                                                            | Management Recommendations                                                                                                                                                                                                                                                  |
|---------------------------------------|---------------------------------------------------------------------------------------------------------------------------------------------------------------------------------------------------------------------|-----------------------------------------------------------------------------------------------------------------------------------------------------------------------------------------------------------------------------------------------------------------------------|
| Cardiac Toxicity                      |                                                                                                                                                                                                                     | See Section 6.2.3.3                                                                                                                                                                                                                                                         |
| Pulmonary Toxicity                    |                                                                                                                                                                                                                     | See Section 6.2.3.2                                                                                                                                                                                                                                                         |
| Infusion-related Reactions            |                                                                                                                                                                                                                     | See Section 6.2.3.1                                                                                                                                                                                                                                                         |
| Drug-related Laboratory Abnormalities | Grade 3 leukopenia or neutropenia                                                                                                                                                                                   | Continue dosing after recovery to $\leq$ Grade 1                                                                                                                                                                                                                            |
|                                       | Grade 2 ALT, AST, or TBIL increased for patients with normal baseline ALT, AST, or TBIL;
Grade 3 or 4 ALT, AST, or TBIL increased lasting $< 7$ days for patients with baseline ALT, AST, or TBIL $> \text{ULN}$ | Dose Interrupted
Resume the treatment if ALT, AST, or TBIL decreased to $\leq$ Grade 1.                                                                                                                                                                                  |
|                                       | Grade 3 ALT, AST, or TBIL increased lasting $\geq 7$ days or Grade 4 ALT, AST, or TBIL increased                                                                                                                    | Permanent discontinuation                                                                                                                                                                                                                                                   |
|                                       | Any other Grade 4 drug-related AE or laboratory abnormality                                                                                                                                                         | Permanently discontinue the treatment with the following exceptions:
1. Individual grade 4 amylase or lipase abnormalities, duration $< 7$ days and no clinical manifestations of pancreatitis;
2. Individual Grade 4 electrolyte imbalance/abnormality, which can be |

|           |                                                                                                  |                                                                                                                                                                                                                                   |
|-----------|--------------------------------------------------------------------------------------------------|-----------------------------------------------------------------------------------------------------------------------------------------------------------------------------------------------------------------------------------|
|           |                                                                                                  | recovered by supplementation/or appropriate treatment within 72 hours;
3. Alkaline phosphatase increased to Grade 4 in patients with bone metastases, and no other relevant organ function changes judged by the investigator. |
| Other AEs | First occurrence of other Grade 3 AEs                                                            | Interrupt the treatment, and resume the treatment if recovered to $\leq$ Grade 1.                                                                                                                                                 |
|           | Second occurrence of the same Grade 3 AE                                                         | Permanent discontinuation                                                                                                                                                                                                         |
|           | Grade 3 AEs that cannot recover to $\leq$ Grade 2 within 7 days or $\leq$ Grade 1 within 14 days | Permanent discontinuation                                                                                                                                                                                                         |
|           | Grade 4 AEs                                                                                      | Permanent discontinuation                                                                                                                                                                                                         |

Permanent discontinuation of KN026 treatment may also be considered for the safety of subjects in some cases of KN026 treatment-related toxicities, including but not limited to:

- Congestive cardiac failure;
- Left ventricular function is significantly decreased;
- Serious infusion reactions, including serious allergic reactions, angioedema, interstitial pneumonia or acute respiratory distress syndrome;
- Pulmonary toxicities, including dyspnea, pneumonia, pneumonitis, pleural effusion, acute pulmonary edema, and insufficiency;
- Cumulatively, medication delay for more than 9 weeks or interruption for more than 3 times.

### Treatment Assignment

The subject will be given a subject number after signing the informed consent form, which will be prepared from small to large in order of dates. Each subject number cannot be reassigned to other subjects once it is determined.

### Packaging and Labeling of Drug

KN046 is aseptically filled in a neutral borosilicate colorless glass vial, and sealed with a halobutyl rubber stopper and an aluminum-plastic cap. Each vial of KN046 liquid formulation contains 1.6 mL of drug solution.

KN026 is aseptically filled in a neutral borosilicate colorless glass vial, and sealed with a halobutyl rubber stopper and an aluminum-plastic cap. Each 10 mL vial contains 50 mg of KN026 lyophilized powder. Each vial is packed in a carton box. Each 20 mL vial of KN026 liquid formulation contains 13 mL of 325 mg of KN026. Each vial is packaged in a carton box.

The bottle label mainly contains the following information: protocol number, drug content and strength, batch number, expiry date, storage conditions, and dosage and administration. The contents of the label will meet the requirements of current regulations.

### **Storage, Transportation and Shelf Life of Drug**

Study drugs should be dispensed to the study site only after receipt of the requisition form in accordance with relevant regulations and the provisions of the sponsor. The drugs should be used in accordance with the following procedures. KN046 and KN026 may not be given until subjects have been enrolled in this trial. Only authorized site personnel can supply or manage the study drugs. In order to ensure the safety of the subjects and to infuse the drugs according to the regimens, the subjects must return to the study site for each dose, and should not carry and use the drugs themselves. The study drugs must be stored in a secure area that is accessible only by the investigator and authorized study site personnel and meets the storage requirements of the study drugs at 2-8°C.

### **Quantity Management of Drug**

The investigator or authorized drug administrator is responsible for the quantity verification, dispensing and record maintenance of the study drug. In accordance with relevant regulatory requirements, the investigator or site designee must maintain a drug accountability record throughout the study. It includes the quantity of study drugs received from the sponsor and the quantity supplied to the subjects.

### **Assessment of Compliance**

Clinical research associates will verify compliance against body weight, group, and other medical records.

### **Occupational Safety**

KN046 and KN026 do not pose an occupational safety risk to site staff under normal compounding and dosing conditions.

## **CONCOMITANT MEDICATIONS AND NON-DRUG THERAPIES**

### **Permitted Medications**

The investigator may administer concomitant medications or treatments according to medical standards from the perspective of the subject's disease treatment needs. All concomitant medications will be recorded on the eCRF form, including drug treatment (e.g., prescriptions, over-the-counter drugs, herbal supplements, IV injection medications, and liquid drugs), and important non-drug therapies (including physical and blood transfusion therapies). Concomitant medications from 28 days prior to the first dose to 30 days after the last dose of KN046 and/or KN026, medication modifications during the study, and treatments received after the 30-day

safety follow-up period for the treatment of KN046- and KN026-related SAEs must be recorded in the eCRF form, including the dose, regimen, route, indication, start and end time of concomitant medications.

Palliative radiotherapy to bone (e.g., local radiotherapy to relieve bone pain, or to prevent the risk of fracture due to lytic lesions) is allowed in this study, but it is required that lesions in the area where palliative radiotherapy to bone are not selected as target lesions and palliative radiotherapy is not intended to treat tumors. PD should be judged based on RECIST 1.1 criteria rather than the need for palliative radiotherapy to bone.

### **Prohibited Medications and Procedures**

Medications that cannot be used concomitantly during the course of the study include:

- Other anti-tumor drugs (e.g., cytotoxic drugs, radical radiotherapy or radiotherapy for the treatment of tumors, immunotherapy, cytokine therapy [except erythropoietin, G-CSF] and endocrine therapy for breast cancer) ;
- Systemic corticosteroids (except for the treatment of immune-related adverse reactions, prophylaxis requiring prior to contrast-enhanced CT angiography due to contrast allergy, alternative therapy at physiological doses, topical hormones [topical, nasal, ocular, inhaled]);
- Immunosuppressants (except for treatment of immune-related adverse reactions);
- Traditional Chinese medicine with anti-tumor indications approved by China Food and Drug Administration (CFDA);
- Other investigational drugs;
- Major surgery (except for diagnostic puncture and peripheral venous catheterization, surgical treatment is the medical routine after the tumor is down-staged);
- RANKL inhibitors (e.g., denosumab) for treatment of bone metastases;
- Botanical drugs that stimulate the immune system (e.g., mistletoe extracts).

If prohibited concomitant medications or procedures are required during the course of the study, subjects should discontinue treatment with KN046 and KN026 (see Section 5.3.1). The investigator may also contact the sponsor to discuss whether the study treatment must be discontinued.

Drugs with clear vital organ toxicity (e.g., liver, kidney, heart) should be avoided whenever possible unless necessary, and alternative drugs should be considered.

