## **CRITERIA FOR WITHDRAWAL OF SUBJECT**

### **Discontinuation of Study Treatment**

Subjects will be required to discontinue treatment with KN046 and/or KN026 if:

- PD judged as per RECIST v1.1 (Note: If the subject's ECOG performance status remains stable and the investigator determines that the subject will benefit from continued treatment with KN046 and KN026, treatment with KN046 and KN026 will be allowed after the first PD judged per RECIST v1.1 criteria, as detailed in Section 6.1.3);
- Significant clinical deterioration (clinical progression), defined as new symptoms or worsening of existing symptoms that are considered clinically significant by the investigator (if PD is not met per RECIST 1.1, the subject needs to continue oncology evaluation);
- Treatment failure requiring urgent use of other anti-tumor drugs (if applicable);
- Unacceptable toxicity (Section 6.1.4) (if study treatment is discontinued due to unacceptable toxicity, the subject needs to continue oncology evaluation);
- Pregnancy;
- Concomitant use of prohibited concomitant medications and procedures as specified in Section 6.2.2, and its consequence is discontinuation of KN046 and KN026;
- Subjects refuse to receive treatment with KN046 and KN026 (if the subject refuses to receive treatment, and PD is not met per RECIST 1.1, the subject will be asked to continue the oncology evaluation);
- Noncompliance.

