Slow infusion of KN046 is strongly recommended for the first 6 doses and prophylactic medications should be given 30 to 60 minutes prior to the first 4 KN046 infusions. Prophylactic medications include combination of H1- and H2-blocker antihistamines (e.g., diphenhydramine and cimetidine) and NSAIDs such as acetaminophen. The recommended prophylactic regimen includes diphenhydramine 25 to 50 mg IM or equivalent PO, cimetidine 400 mg IV infusion, and acetaminophen 500-1000 mg PO. Steroids are generally not recommended as part of routine prophylactic regimens, and are used only if necessary. Montelukast may be included in the prophylactic regimen if the patient experiences symptoms of spasm bronchial. If there is no infusion-related reaction after the 4th infusion, prophylactic medications for subsequent doses should be administered at the discretion of the investigator. In vitro studies showed that KN046 caused strong immunostimulatory effects. In combination with platinum-based doublet chemotherapy, a certain proportion of infusion-related reactions and increased inflammatory

factors (IL-6, IL-10) were observed after Dose 2 of KN046; the proportion of infusion reactions decreased rapidly with the increased number of doses. For subjects who experience  $\geq$  Grade 2 treatment-related AEs of KN046 after Dose 1, it is recommended to determine IL-6 levels before the next dose. If IL-6 levels increase, pretreatment with tocilizumab 160 mg (intravenous infusion 1-2 hours prior to KN046 administration) is allowed after consultation with the sponsor's Medical Department; for subjects who experience  $\geq$  Grade 2 IRRs during the administration of KN046, it is recommended to determine IL-6 levels immediately, and 160 mg tocilizumab treatment is allowed on the basis of routine clinical management. After IRR recovery, resuming slow KN046 administration (at least 50% reduction in infusion rate) under respiratory, ECG, and blood pressure monitoring conditions is allowed.

Severe hypersensitivity reactions could manifest as airway injury, decreased oxygen saturation (less than 90%), confusion, lethargy, hypotension, pale skin/clamminess, and cyanosis.

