| Grade 1     | 
 
Lung CT scans, and required pulmonary function testing includes: spirometry, DLCO, and oxygen saturation at rest.
 
Chest X-ray or CT scan will be repeated every 6 weeks until return to baseline.
 
                                                                                                                  | 
 
Exclude source of infection
 
No special treatment is required
 
                                              | 
 
Maintain the original dose
 
                                                                                                                                                                                                                                                                                           |
| Grade 2     | 
 
Lung CT scans, and required pulmonary function testing includes: spirometry, DLCO, and oxygen saturation at rest.
 
Repeat chest X-ray or CT scan every 3 to 4 weeks (in a treatment cycle) until return to baseline.
 
                                                                                                | 
 
Exclude source of infection
 
Hormonal therapy if cough is evident
 
                                          | 
 
Resume the original dose of KN026 after recovery to <math>\leq</math> Grade 1. If cough persists, hold KN026 until recovery to <math>\leq</math> Grade 1.
 
Permanently discontinue KN026 if the subject fails to recover to <math>\leq</math> Grade 1 within 3 weeks after appropriate medical intervention.
 
 |

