| Grade 3     | 
 
Lung CT scans, and required pulmonary function testing includes: spirometry, DLCO, and oxygen saturation at rest.
 
Repeat chest X-ray or CT scan every 3 to 4 weeks (in a treatment cycle) until return to baseline.
 
Consultation with a pulmonologist for bronchoscopy (biopsy or bronchoalveolar lavage)
 
 | 
 
Exclude source of infection
 
Administer hormonal therapy and gradually reduce the dose as medically judged
 
 | 
 
Hold KN026 until recovery to <math>\leq</math> Grade 1.
 
If a subject has clinical benefit, the original dose of KN026 can be maintained (recovered to <math>\leq</math> Grade 1 within 3 weeks) after recovery to <math>\leq</math> Grade 1.
 
                                                                |
| Grade 4     | 
 
Lung CT scans, and required pulmonary function testing includes: spirometry, DLCO, and oxygen saturation at rest.
 
Repeat chest X-ray or CT scan every 3 to 4 weeks (in a treatment cycle) until return to baseline.
 
Consultation with a pulmonologist for bronchoscopy (biopsy or bronchoalveolar lavage)
 
 | 
 
Exclude source of infection
 
Administer hormonal therapy and gradually reduce the dose as medically judged
 
 | 
 
Permanently discontinue KN026
 
                                                                                                                                                                                                                                                                                        |

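### Sections 6.2.2 and 5.3.1 stop both drugs for steroid use that Table 5 and Section 6.1.4.1 direct or accept before treatment resumes

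*Protocol*

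**What the plan says.** **The prohibition (Protocol, Section 6.2.2).** The steroid entry begins "Systemic corticosteroids (except for the treatment of immune-related adverse reactions, prophylaxis requiring prior to contrast-enhanced CT angiography due to contrast allergy" and goes on to except physiological replacement and topical, nasal, ocular and inhaled use. The consequence is stated as "If prohibited concomitant medications or procedures are required during the course of the study, subjects should discontinue treatment with KN046 and KN026", followed by "The investigator may also contact the sponsor to discuss whether the study treatment must be discontinued".

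**The matching criterion (Section 5.3.1).** The list of events for which treatment is required to stop includes "Concomitant use of prohibited concomitant medications and procedures as specified in Section 6.2.2, and its consequence is discontinuation of KN046 and KN026". It does not mention a discussion with the sponsor.

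**KN026 pneumonitis (Section 6.2.3.2, Table 5).** At Grade 2 the management column reads "Hormonal therapy if cough is evident", and at Grade 3 "Administer hormonal therapy and gradually reduce the dose as medically judged". Both rows provide for KN026 again at the original dose after recovery to Grade 1 or lower. At Grade 3 this is conditional on clinical benefit and recovery within 3 weeks.

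**KN046 restart (Section 6.1.4.1).** When a treatment-related toxicity has needed hormones, KN046 may restart once the dose is at or below 10 mg/day prednisone or equivalent. This text is not limited to immune-related toxicity.

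**Infusion reactions (Section 6.2.3.1).** Steroids are not part of routine prophylaxis but may be used where needed. For a raised IL-6, "pretreatment with tocilizumab 160 mg (intravenous infusion 1-2 hours prior to KN046 administration) is allowed" after consultation with the sponsor's medical department.

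**The concern.** The toxicity sections give a steroid and then plan for further dosing. The prohibited-medication rule treats the same steroid, unless an exception covers it, as a reason to stop both drugs. If the exceptions do not cover it, an investigator cannot follow both texts.

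Discontinuation and exposure are themselves outcomes here. Section 9.6.1 evaluates tolerability by the number of subjects with interruption, delay and discontinuation, lists the reasons, and summarises dose intensity and relative dose intensity. If sites follow different sections for the same clinical course, those tables partly reflect how the protocol was read as well as how the regimen was tolerated. In cohorts of 20 to 60 subjects, a few such cases would be visible.

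**Working it through.** No sample size, error rate or event count is involved. The check sets the texts side by side for the same subject.

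1. **Is hormonal therapy a corticosteroid here?** Yes. Section 6.1.4.1 expresses the hormone dose in prednisone equivalents. Table 5 gives no route, but its Grade 3 row describes a taper, which points to systemic use.

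2. **Does a 6.2.2 exception cover it?** The only exception for treating a reaction is the immune-related one. The protocol keeps KN026 pneumonitis separate. Section 6.2.3.2 attributes it to HER2-targeted therapy and Table 5 to KN026, while immune-related pneumonia is listed under KN046 in Sections 6.1.4.1 and 8.2.2. Nothing calls the Table 5 event immune-related.

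3. **What does each section tell the site to do?**

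| Situation | 6.2.2 / 5.3.1 | Toxicity section | Result |
|---|---|---|---|
| KN026 pneumonitis, Grade 3 | Steroid not excepted; stop both drugs | Table 5 directs the steroid; original KN026 dose possible after recovery | Direct conflict |
| KN026 pneumonitis, Grade 2 with evident cough | Same | Table 5 gives the steroid; original dose resumes after recovery | Direct conflict |
| KN026 pneumonitis, Grade 4 | Same | Table 5 stops KN026 for good; 6.1.4.2 leaves KN046 to the investigator | Differ on one drug or both |
| KN046-related toxicity, not immune-related, needing a steroid | Same | 6.1.4.1 lets KN046 restart after taper | Direct conflict |
| Steroid prophylaxis before a later infusion | Only contrast-allergy prophylaxis is excepted | 6.2.3.1 permits it where needed; dosing goes on | Conflict, over a permitted use |
| Tocilizumab | "Immunosuppressants (except for treatment of immune-related adverse reactions") | 6.2.3.1 allows it; KN046 may follow | Conflict only if it counts as an immunosuppressant, which is not stated |

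4. **What reaches the analysis?** Exposure, dose intensity, and the discontinuation counts and reasons are affected directly. Response assessment is not: footnote 13 to Table 1 requires imaging to continue after a stop without radiographic progression, until progression, new anti-tumor therapy, withdrawal of consent or loss to follow-up. An effect on ORR or DOR could arise only through lost exposure or an earlier switch of therapy.

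5. **Can the number affected be derived?** No. Section 1.3.3 reports one treatment-related Grade 2 interstitial pneumonia SAE among 63 subjects on KN026 alone (1/63 = 1.6%). That shows the situation can arise. It does not say whether a steroid was given, and the regimen differs from the one studied here.

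**The case against.** The strongest defence is that stopping is not automatic. Section 6.2.2 says that subjects should discontinue and at once offers a discussion with the sponsor. The 5.3.1 entry refers back to 6.2.2 and can be read as applying only where that process ends in discontinuation. An express direction in a toxicity table can also be read as overriding a general prohibition, and a site treating with both drugs could class a pneumonitis as immune-related and use the exception.

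Part of this stands. A reader might infer that the protocol forces both drugs to stop; the sponsor-discussion sentence means it does not. But 5.3.1 omits the option, Table 5 requires no contact with the sponsor before KN026 resumes, and no sentence says which section takes precedence. Discretion makes the outcome case by case without reconciling the texts. The immune-related route does not help where the event is attributed to KN026 alone.

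Three further inferences are tempting but unsupported:

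- **That the infusion-reaction section prescribes prohibited drugs.** It only permits steroids and tocilizumab. Tocilizumab is not classified anywhere in the document, and its use as pretreatment already requires sponsor consultation.
- **That the dexamethasone provisions contradict resumption.** Section 6.2.3 only requires the drug to be on hand. Section 6.2.3.1 directs it for severe hypersensitivity, where Table 4 already ends treatment with the drug at Grade 3 or 4. A note allows KN046 rechallenge to be discussed with the sponsor. What remains is mainly whether one drug or both stop.
- **That the affected number follows from infusion-reaction rates.** Applying 17.0% to 80 subjects gives 13.6, and 52.9% to 122 gives 64.5. These rates come from KN046 alone and from KN046 with paclitaxel and carboplatin. Table 4 asks only for a slower infusion at Grade 1, and the share given a steroid or tocilizumab is not reported. In the 32 subjects given KN026 with KN046 in KN046-IST-02, infusion reactions are not among the listed related events at 15% or more.

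**Conclusion.** The point holds as an inconsistency of wording that leads to opposite treatment decisions. It is clearest for pneumonitis attributed to KN026 at Grade 3, or at Grade 2 with evident cough, and for KN046 restart after steroid treatment of a toxicity that is not immune-related. Steroid prophylaxis before infusions is a minor addition, and tocilizumab raises the question only if it is an immunosuppressant.

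The effect falls on exposure, discontinuation counts and reasons, and the tolerability summaries. A reader might infer that the primary endpoints are compromised; continued imaging means any such effect is indirect. The number of subjects cannot be stated from the document, and the conclusion does not depend on it. The conclusion assumes that hormonal therapy in Table 5 is systemic and that KN026 pneumonitis is not automatically immune-related. Both follow the protocol's own usage but are not stated outright. The point should be corrected, although it does not threaten the design.

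**What to change.** Reconcile Sections 6.2.2 and 5.3.1 with Sections 6.1.4.1 and 6.2.3.1 and Table 5, so that one stated rule says whether steroid use directed or permitted by the toxicity sections triggers discontinuation and, if so, of one drug or both. Carry the sponsor-discussion option of 6.2.2 consistently into 5.3.1. State whether tocilizumab falls under the immunosuppressant entry. Which rule governs is for the sponsor to decide; this review takes no position on the clinical management.

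The cost is wording and cross-references in the affected sections. No visit, procedure or subject is added. Recorded discontinuations and their reasons would then rest on the same rule at every site.
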